#### Follow-up duration and participant timeline

The baseline visit includes collection of medical history, a physical examination, evaluation of symptoms and signs, laboratory tests, a 12-lead electrocardiogram, visual acuity assessment, assessment for peripheral neuropathy, smear, culture, and the Xpert MTB/XDR assay. During the treatment period, follow-up visits are scheduled monthly until treatment completion. After treatment, visits are conducted every three months in the first six months, and then every six months until 21 months after randomisation. Additional visits could be conducted as clinically needed. Follow-up assessment during treatment and post-treatment assessment are shown in Table 3. MTB strains are collected and sent to the central lab for whole genome sequencing at baseline and post-baseline visits as needed.

**Table 3 Tab3:** Schedule of enrolment, interventions, and assessments

	Baseline	Treatment Period						Post-treatment Period		
		monthly						M12	M15	EOS^#^
Timepoint (month)	-2 weeks to M0	M1	M2	M3		…	EOT^**^			
Inform consent	**×**									
Eligibility assessment	**×** ^*****^									
Treatment allocation	**×**									
Susceptibility testing for rifampicin	**×**									
Rapid molecular test for FQ resistance	**×**									
Treatment adherence assessment		**×**	**×**	**×**		**×**	**×**			
Evaluation of signs and symptoms	**×**	**×**	**×**	**×**		**×**	**×**	**×**		**×**
Sputum Tests (smear and culture)	**×**	**×**	**×**	**×**		**×**	**×**	**×**		**×**
Electrocardiogram	**×**	**×**	**×**	**×**		**×**	**×**	if indicated		
Routine blood tests and chemistry	**×**	**×**	**×**	**×**		**×**	**×**	if indicated		
Chest Radiography	**×**	if indicated			**×**			if indicated		
Haemoglobin A1c	**×**	Every three months in participants with diabetes								
TSH, FT3, FT4	**×**	monthly if on prothionamide								
HIV test, hepatitis B and C	**×**									
Pregnancy test	**×**									
Visual acuity assessment	**×**	if indicated						if indicated		
Assessment for peripheral neuropathy	**×**	if indicated						if indicated		
SDS and SAS	**×**	if indicated						if indicated		

Abbreviation: EOT: end of treatment; EOS: end of study; TSH: thyroid-stimulating hormone; FT3: free triiodothyronine; FT4: free thyroxine; SDS: self-rating depression scale; SAS: self-rating anxiety scale

^*^ Sputum rapid molecular test for rifampicin resistance should be performed during screening for eligibility assessment, and rapid molecular test for fluoroquinolone resistance should be acquired before randomisation for stratification

^**^ Timepoint of EOT in Regimen A1, A2, A3, A4, A5 and B1 is 9 months. Timepoint of EOT in Regimen B-SOC is 20 months

^#^ Timepoint of EOS is 21 months after randomisation

#### Treatment compliance

At each visit, study medications are prescribed and dispensed to participants by a research nurse or doctor to ensure correct treatment. Each participant is provided with a medication diary for self-documentation. During follow-up visits, comprehensive adherence assessments are conducted by research doctors, verifying drug types, dosages, and any missed or incorrect doses, with all data recorded in the case report form. Additionally, the central research team conducts regular cross-checks with site investigators to verify the total medication consumption for each participant to address any instances of missed or reduced doses.

#### Sample size assumptions

The sample size calculation was performed in PASS 11 system (NCSS, Version 11.0.10). In an individual patient data meta-analysis of 13,273 MDR/RR-TB patients from 38 countries, the treatment success rate of the bedaquiline-containing oral shorter regimen is 73% [16]. We thus assume a 70% favourable rate in the control arm and 80% in the experimental arms in fluoroquinolone susceptible patients. Since multiple experimental groups are simultaneously compared with the control group, the family-wise type I error will be controlled by a fixed sequence approach. The experimental groups are tested sequentially in a pre-specified order, and if any group fails to demonstrate non-inferiority, testing for subsequent groups will be discontinued. All the previous comparisons will be done at the one-sided alpha level of 2.5%. Therefore, a sample size of 73 per arm will afford 80% power to establish non-inferiority of seven experimental regimens with a non-inferiority margin of 10% at a one-sided α level of 2.5%. The number excluded from the modified intention-to-treat population is estimated to be 30% and therefore the recruitment target is increased to 104 per arm. The total sample size of fluoroquinolone-susceptible RR-TB participants is 832.

By November 2024, randomisation to regimen A2b, A2c as well as A5 has been ceased following protocol amendment. The actual number of enrolled participants at the time of early closure were 73, 72, 92 respectively in regimen A2b, A2c and A5. Therefore, the total sample size of fluoroquinolone-susceptible RR-TB participants have been adjusted to 520 (including regimen A1, A2a, A3, A4 and A-SOC).

In fluoroquinolone-resistant RR-TB participants, we assume that 75% of participants in the experimental arm (regimen B1) and 65% of participants in the control arm (regimen B-SOC) will achieve a favourable outcome. A sample size of 82 per arm will afford 80% power to establish non-inferiority with a margin of 10% and a one-sided α level of 0.025. The number excluded from the modified intention-to-treat population is estimated to be 30% and therefore the recruitment target is increased to 117 per arm. The total sample size of fluoroquinolone-resistant participants is 234.

As of September 2025, enrolment for the fluoroquinolone-resistant group has completed, while recruitment of fluoroquinolone-susceptible participants remains ongoing.

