**Methods:**

INSPIRE TB is a pragmatic, multicentre, randomised, controlled, non-inferiority open-label trial to evaluate novel regimens in pulmonary RR-TB patients of 16–75 years old with or without fluoroquinolone resistance. Before randomisation, an individualized assessment is conducted, considering drug susceptibility, contradictions, tolerance. Eligible participants are randomised based on fluoroquinolone susceptibility results from the Xpert MTB/XDR assay. Participants susceptible to fluoroquinolones are randomised to receive either one of seven different nine-month oral regimens or a nine-month standard-of-care regimen as the control. The experimental arms are five-drug regimens, each consisting of five agents selected from the following: bedaquiline, linezolid, a fluoroquinolone, cycloserine, clofazimine and pyrazinamide. Fluoroquinolone-resistant participants are randomised to either a 9-month oral regimen (bedaquiline, cycloserine, clofazimine, linezolid and pyrazinamide), or a 20-month conventional regimen as control in a 1:1 ratio. The primary outcome is the proportion of participants with a favourable outcome (two negative culture for *Mycobacterium Tuberculosis*, the latest sample collected between month 21 and 23) at 21 months after randomisation in the modified intention-to-treat population, measured in fluoroquinolone-susceptible and fluoroquinolone-resistant participants respectively. A sample size of 832 fluoroquinolone-susceptible RR-TB patients and 234 fluoroquinolone-resistant RR-TB patients afford 80% power to establish non-inferiority with a non-inferiority margin of 10% at a one-sided α level of 2.5%. The type I error will be controlled with a fixed-sequence approach.

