#### Randomisation

Randomisation is based on an online system (REDCap) operated remotely at Huashan Hospital, Fudan University and is stratified by research sites. Prior to randomisation, patient eligibility is re-confirmed through a comprehensive review of medical history. An individualized eligibility assessment was documented in the electronic case report form, capturing detailed data on drug susceptibility, contraindications, concomitant medications, and treatment tolerance, as specified in the Supplementary Materials. Patients with known resistance or contraindications to regimen components are excluded from the randomisation procedure and receive guideline-based standard care. Eligible participants will be stratified into fluroquinolone-susceptible arms (group A) and fluoroquinolone-resistant arms (group B) based on baseline Xpert MTB/XDR results.

In group A, the randomisation ratio between the regimen A-SOC and each experimental arm is 1:1. Enrolment into the experimental arm will be ceased once its planned sample size is reached. Participants resistant to fluoroquinolones are randomised to regimen B1 and regimen B-SOC in a 1:1 ratio.

In response to updated RR-TB treatment guidelines and emerging evidence, this trial was strategically optimized in 2024. The initial design included a bedaquiline-free arm (regimen A5). Following WHO’s endorsement of bedaquiline-based oral shorter regimens [13, 14], the study protocol was amended in version 6.0 (November 2024) to discontinue the enrolment of regimen A5, ensuring sufficient sample size for evaluation of bedaquiline-containing arms. In addition, randomisations to regimen A2b and A2c were halted based on two primary considerations. First, a recently published multicentre randomised controlled trial demonstrated the non-inferior efficacy of a nearly identical structured linezolid dose-reduction strategy [15], thereby compromising the novelty of our pre-planned analysis. Second, enrolment has progressed more slowly than we initially anticipated. Therefore, a strategic decision was made to concentrate limited resources to prioritize the remaining arms to address critical evidence gaps in RR-TB treatment.

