The primary efficacy analysis will be conducted in the mITT population, and efficacy outcomes will be reported as supportive analyses from both the PP and ITT populations. The absolute between-group difference with 95% confidence interval (CI) in the proportion of participants with a favourable outcome will be calculated. The non-inferiority of an experimental arm versus the control arm will be established if the upper bound of the 95% CI is less than 10% (the margin of non-inferiority). In group A, multiple experimental arms are compared to the control regimen. Type I error rate will be controlled with a pre-planned fixed sequence method. First, the regimen with the highest expected treatment success rate will be compared to the control. If non-inferiority is established, comparisons will proceed sequentially to the next experimental regimen in descending order of expected efficacy. For any regimen that demonstrates non-inferiority, a subsequent test for superiority over the control will be performed.

Patient characteristics will be described with median and range (or interquartile range), or numbers and percentages. The median time to smear and culture conversion will be estimated in each arm using the Kaplan-Meier method and between-group difference will be compared with the log-rank test. Proportion of participants with any grade 3–5 adverse event, any serious adverse event (SAE) and any treatment-related SAE will be described with numbers and percentages.

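### The stated 80% power for the fluoroquinolone-susceptible regimens is single-comparison power; under the fixed sequence only the first regimen tested has it, and the fourth has about 55%

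*Protocol article*

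**What the plan says.** The Sample size assumptions section of the protocol article sets the planning values: "We thus assume a 70% favourable rate in the control arm and 80% in the experimental arms in fluoroquinolone susceptible patients". The margin is 10 percentage points and every step is tested at the full one-sided 2.5%. The experimental arms are tested in a pre-specified order, and "if any group fails to demonstrate non-inferiority, testing for subsequent groups will be discontinued". The section then concludes, with the word 'Therefore', that "a sample size of 73 per arm will afford 80% power to establish non-inferiority of seven experimental regimens".

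Statistical considerations and analysis population repeats the rule: "comparisons will proceed sequentially to the next experimental regimen in descending order of expected efficacy". Randomisation describes one control arm shared by all comparisons: "the randomisation ratio between the regimen A-SOC and each experimental arm is 1:1".

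After the amendment that closed A2b, A2c and A5, the sample size section lowers the target to 520, for A1, A2a, A3, A4 and A-SOC. It does not restate the power. The Abstract still reads "A sample size of 832 fluoroquinolone-susceptible RR-TB patients and 234 fluoroquinolone-resistant RR-TB patients afford 80% power to establish non-inferiority".

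**The concern.** A fixed sequence spends no alpha, so each test keeps its full 2.5% and no enlargement is needed on that account. It does cost power. The second regimen can succeed only if the first has, the third only if the first two have, and so on. A single figure of 80%, stated after the stop rule and attached to seven regimens, leaves out that cost.

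What is at stake is how the result is read. A regimen late in the order may be left without a formal conclusion because an earlier one failed, or because the control arm happened to do well. If the published power is 80%, such a result looks more informative than it is. The Discussion presents the trial as a source of evidence on four regimens, so the chance of establishing all four matters to its readers.

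**Working it through.** **Inputs** (Sample size assumptions unless noted)
- Control rate 0.70; rate in every experimental arm 0.80.
- Margin 0.10; one-sided 2.5% at each step.
- 73 evaluable per arm; 104 recruited, with 30% excluded from the mITT population.
- One shared control arm, 1:1 with each experimental arm (Randomisation).
- Testing stops at the first failure.

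**Step 1: the plan's own figure**

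For one comparison with unpooled variance, the distance from the margin is 0.80 − 0.70 + 0.10 = 0.20.

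n = (1.96 + 0.8416)² × (0.70×0.30 + 0.80×0.20) / 0.20² = 7.849 × 0.37 / 0.04 = 72.6, so 73.

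This matches the plan. Power of one comparison at n = 73: the standard error is √(0.37/73) = 0.0712, and Φ(0.20/0.0712 − 1.96) = Φ(0.849) = 80.2%. Exact binomial calculation gives 80.6% with the Wald test and 79.8% with a score test. So 73 is a pairwise size, with nothing added for the sequence.

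**Step 2: power at position k**

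Given the control count c, the experimental arms are independent and, on the planning values, identical. Hence

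power(k) = Σ over c of P(c) × [P(one arm passes | c)]^k,

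with c binomial(73, 0.70) and each experimental count binomial(73, 0.80).

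| Position | Exact, Wald test | Exact, score test | Normal approximation |
|---|---|---|---|
| 1 | 80.6% | 79.8% | 80.2% |
| 2 | 69.1% | 67.8% | 69.8% |
| 3 | 61.1% | 59.7% | 63.0% |
| 4 | 55.2% | 53.7% | 58.0% |
| 7 | 43.6% | 42.5% | 48.4% |

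A simulation of 2 million trials with the Wald test gives 80.6, 69.0, 61.1, 55.1 and 43.6% at the same positions.

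The last position reached is also the chance of establishing every regimen up to it: about 55% for the current four, about 44% for seven.

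**Step 3: why not 0.8 to the power k**

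Independent comparisons would give 0.8⁴ = 41%. The shared control makes the comparisons positively correlated, at about 0.21/0.37 = 0.57, which lifts the fourth position to about 55%.

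**Step 4: does the amendment change this?**

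832/8 = 104 and 520/5 = 104, so recruitment per arm is the same. With 30% excluded, 104 × 0.70 = 72.8, close to 73. The per-position figures therefore apply to the current target, and the amendment only shortens the sequence from seven to four.

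**The case against.** The best reply is that 80% was meant as per-comparison power, which is a common convention, and that 'Therefore' means only that no alpha is split and the pairwise size stands. That explains where 73 comes from. It does not rescue the sentence, which never says per comparison, follows directly on the stop rule and names seven regimens. Under that rule a regimen that is never reached cannot be declared non-inferior.

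A second reply is that testing runs in descending order of expected efficacy, so the 80% given to every arm may be only a common planning value. This stands as a condition on the figures. As an illustration with assumed true rates of 85, 83, 81 and 79% against a 70% control, exact Wald power by position is about 96, 89, 78 and 65%. The loss with position remains, but its size depends on the true rates.

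Third, the analysis section promises a difference with a 95% confidence interval, so readers would see more than a failed test. That softens the consequence but does not correct the power figure.

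Several stronger readings are tempting and not supported:
- That 73 was miscalculated, or that type I error is uncontrolled. The size reproduces, and the sequence holds the error rate.
- That a particular regimen, say A4, has 55% power. The article does not list the order, so positions cannot be tied to named arms. The full protocol may list it, so its absence here is not a fault.
- That 832 in the Abstract is part of the power error. It is a figure not updated after the amendment; the sample size section itself gives 520.
- That the fixed sequence should be replaced. Hochberg's procedure at the same planning values gives about 74% for each of four regimens, against an average of about 66% now. But the first regimen falls from about 81% to 74%, and the chance of establishing all four stays at about 55%. That is a trade-off, not a clear correction.

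**Conclusion.** The point holds as a misstatement of what the 80% covers. The figure is right for a single comparison and, under the stated sequence, for the first regimen tested only. For the four current regimens, power by position is about 81, 69, 61 and 55%, with 54 to 58% for the fourth depending on method. That is up to about 25 points below the stated figure.

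These values rest on the plan's own assumptions: 70% on control, a true 80% in every experimental arm, 73 evaluable per arm and a shared control. They would differ if the true rates differ between arms.

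**What to change.** In Sample size assumptions:
- State that 73 per arm gives 80% power for a single comparison, and that under the sequence only the first regimen tested attains it.
- Give power by position in the pre-specified order (about 81, 69, 61 and 55%) and the chance of establishing all four (about 55%), labelled as conditional on equal 80% rates.
- Tie these figures to the current target of 520, four experimental arms plus control.

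In the Abstract, replace 832 with 520 and describe the 80% in the same way.

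The cost is a few sentences and a less favourable stated power. If the sponsor wanted 80% at the fourth position, about 110 evaluable per arm would be needed (80.6% by the exact Wald calculation), but the correction does not depend on that.

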#### Outcome measurements

The primary efficacy outcome is the proportion of participants with a favourable outcome at 21 months after randomisation. The primary analysis will be conducted in the modified intention-to-treat (mITT) population in fluoroquinolone-susceptible and fluoroquinolone-resistant arms respectively. Definition of treatment outcomes is summarized in Table 4.

**Table 4 Tab4:** Definitions of primary outcome

Outcome definitions
**Favourable outcome**: The outcome will be classified as favourable if not previously classified as unfavourable, and one of the following is true: (1) The last two culture results are negative. These two cultures must be taken from respiratory samples collected on separate visits at least 7 days apart. The latest culture sample collected between month 21 and 23. (2) The last culture result (from a respiratory sample collected between month 21 and 23) is negative; and there is no other post-baseline culture result; and bacteriological, radiological and clinical evaluation is favourable. (3) There is no culture result collected between month 21 and 23 or the result of that culture is positive due to laboratory cross contamination; and the most recent culture result is negative; and bacteriological, radiological and clinical evaluation is favourable.
**Unfavourable outcome**: (1) At least one of the last two cultures (taken from respiratory samples collected on separate visits at least 7 days apart) is positive and laboratory cross contamination is ruled out. The latest between month 21 and month 23. (2) There is no culture result collected between month 21 and 23 or the result is positive due to laboratory cross contamination; and - bacteriological, radiological and clinical evaluation is unfavourable. OR - the most recent culture result is positive in the absence of laboratory cross contamination. (3) There is no culture result collected between month 21 and 23 or the result is positive due to laboratory cross contamination; and - either there is no other post-baseline culture result, or the penultimate culture result is positive due to laboratory cross contamination. OR - bacteriological, radiological and clinical evaluation is not available. (4) The last culture result (from a respiratory sample collected between month 21 and 23) is negative; and either there is no other post-baseline culture result, or the penultimate culture result is positive due to laboratory cross contamination; and bacteriological, radiological and clinical evaluation is unfavourable. (5) The last culture result (from a respiratory sample collected between month 21 and 23) is negative; and either there is no other post-baseline culture result, or the penultimate culture result is positive due to laboratory cross contamination; and bacteriological, radiological and clinical evaluation is not available. (6) Participant whose treatment regimen needed to be terminated or permanently changed ^a^ to a new regimen. (7) Treatment extension that does not meet protocol-defined extension criteria. (8) Initiation of a new RR-TB treatment regimen after the end of the allocated study regimen and before month 21 (relapse). (9) Loss to follow-up ^b^. (10) Death from any cause.

^a^ A permanent regimen change is constituted by any of the following: [1] adding or replacing two or more drugs in the allocated regimen; [2] adding second-line injectables in the allocated regimen; [3] replacing a group C drug with a group B drug (clofazimine, cycloserine) not originally included; [4] replacing a group B drug with a group A drug (moxifloxacin, levofloxacin, linezolid, bedaquiline) not originally included

^b^ Loss to follow-up is defined in case that a participant fails to complete two or more consecutive scheduled visits and cannot be reached after at least three phone calls and one home interview

Main secondary outcomes are measured in fluoroquinolone-susceptible and fluoroquinolone-resistant arms respectively. Secondary outcomes are defined as follows:

Time to sputum smear conversion in the mITT population.Time to sputum culture conversion in the mITT population.The proportion of participants with a favourable outcome at 21 months post-randomisation in the per-protocol (PP) population.The proportion of participants with grade 3 or higher adverse event (AEs), serious adverse events (SAEs) at 21 months post-randomisation in the safety population.All-cause mortality and treatment relevant mortality at 21 months post-randomisation in the safety population.The proportion of participants with treatment relevant SAEs at 21 months post-randomisation in the safety population.The proportion of participants with grade 3 or higher QTc prolongation in the safety population.The proportion of participants experiencing permanent drug discontinuation or replacement due to QTc prolongation in the safety population.

Exploratory outcome measures are defined as the following:

The proportion of participants with a favourable outcome at 21 months after randomisation in regimen A2a, A2b and A2c in the mITT population.The proportion of participants with grade 3 or higher myelosuppression, peripheral neuropathy and optic neuropathy in regimen A2a, A2b and A2c in the safety population.The proportion of participants with linezolid discontinuation or dose reduction due to AE in regimen A2a, A2b and A2c in the safety population.

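### Table 4 stops counting retreatment at month 21 although the deciding culture may be taken up to month 23, so a few retreated relapses can be scored favourable

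*Protocol article*

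**What the plan says.** All references are to the protocol article.

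- **Retreatment rule** (Outcome measurements, Table 4, unfavourable item 8): "Initiation of a new RR-TB treatment regimen after the end of the allocated study regimen and before month 21 (relapse").
- **Culture rule** (Table 4, favourable rule 1): "The last two culture results are negative". The two samples come from separate visits at least 7 days apart, and the second has its own window: "The latest culture sample collected between month 21 and 23". Rule (1) sets no clinical, imaging or retreatment condition, whereas favourable rules (2) and (3) also require a favourable evaluation.
- **Precedence** (Table 4, opening of the favourable definition): "The outcome will be classified as favourable if not previously classified as unfavourable".
- **Visits** (Follow-up duration and participant timeline): after treatment, "visits are conducted every three months in the first six months, and then every six months until 21 months after randomisation". The footnote to Table 3 adds "Timepoint of EOS is 21 months after randomisation". Unscheduled contact is possible: "Additional visits could be conducted as clinically needed".

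**The concern.** Item (8) is the only item in Table 4 that names a new regimen started after the allocated one has ended, and it closes at month 21. The last scheduled visit is at month 21, so a regimen decided there cannot start in time to count. The culture that decides the outcome may be taken up to two months later.

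The same clinical course can therefore be scored differently according to whether retreatment begins just before or just after month 21. A culture taken on the new drugs may also help to classify the allocated regimen as successful. The trial is open-label, and the Discussion accepts that assessment bias is possible. A primary endpoint that turns on the start date of a clinician's decision is exposed to that bias.

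**Working it through.** **Visit dates.** For a 9-month arm, post-treatment visits fall at 9 + 3 = 12, 12 + 3 = 15 and 15 + 6 = 21 months, in line with Table 3. A relapse arising after month 15 is first seen on schedule at month 21, unless an unscheduled visit finds it sooner. B-SOC ends treatment at month 20, so item (8) covers 21 − 20 = 1 month there, against 21 − 9 = 12 months in B1.

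**Table 4 applied as printed**, with no laboratory cross-contamination:

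| Case | Cultures (month) | Evaluation | New regimen starts | Rule met | Score |
|---|---|---|---|---|---|
| a | 15 neg, 21 pos | unfavourable | 21 | unfavourable (1) | unfavourable |
| b | 15 neg, 21 pos, 22 neg | unfavourable | 21.5 | unfavourable (1) | unfavourable |
| c | 12 neg, 15 neg, none in 21–23 | unfavourable | 21 | unfavourable (2) | unfavourable |
| d | 15 neg, 21 neg | unfavourable | 21 | favourable (1) only | **favourable** |
| d′ | as d | unfavourable | 20.9 | unfavourable (8) | unfavourable |
| e | 15 neg, 21 pos, 22 neg, 22.5 neg | unfavourable | 21.5 | favourable (1) | **favourable**, unless already fixed as unfavourable |

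**Case d.** Items (2) and (4) use the evaluation only when a usable window culture or a usable earlier culture is missing. Neither is missing here. Item (6) concerns ending or changing the allocated regimen and does not clearly reach a new regimen begun after it has finished. Only favourable (1) remains. Cases d and d′ differ only in the start date of the new regimen.

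**Case e.** At month 21 the positive culture meets unfavourable (1). If classification is made then and held, the precedence clause keeps the participant unfavourable. If it is made once, on the last two cultures available, favourable (1) applies. Table 4 does not say which. The two later cultures would need unscheduled visits.

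**Scale.** The planned numbers after mITT exclusions (Sample size assumptions) reproduce from n = (1.960 + 0.842)² × [p₁(1 − p₁) + p₂(1 − p₂)] / (p₂ − p₁ + 0.10)²:

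- Group A, 70% and 80%: 7.85 × (0.21 + 0.16) / 0.04 = 72.6, so 73 per arm, as stated.
- Group B, 65% and 75%: 7.85 × (0.2275 + 0.1875) / 0.04 = 81.4, so 82 per arm, as stated.

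One reclassified participant is therefore 1/73 = 1.4 points in a Group A arm, or 1/82 = 1.2 points in a Group B arm. The documents give no relapse rate and no count of such cases.

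**The case against.** The strongest defence is that month 21 is the endpoint itself. The primary outcome is defined at 21 months, the study ends then, and months 21 to 23 only allow time to collect the last culture. Stopping event counting at the endpoint is a legitimate choice. It does not explain, however, why a relapse recognised at the endpoint visit should be left out while a culture taken after that visit is allowed to decide.

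Second, the common relapse is already caught. A reader might infer that any relapse found and retreated at the final visit escapes. Cases a to c show otherwise: a positive culture among the last two is unfavourable whatever the retreatment date, and an unfavourable evaluation with no usable window culture is unfavourable too. This stands and limits the point to cases d and e.

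Third, the Discussion says that outcomes must be backed by recorded culture, imaging and clinical evidence. That is a general safeguard; it does not override a rule under which two negative cultures suffice.

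Fourth, unscheduled visits may detect a symptomatic relapse before month 21. That reduces the number of cases but does not settle how the remaining ones are scored.

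Fifth, simply moving the cut-off to month 23 would capture later retreatment only in participants who happen to return, which is uneven ascertainment in an open-label trial. This is a good reason to tie the cut-off to each participant's own final assessment.

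**Conclusion.** The point holds in a narrow form. Table 4 uses different end dates for retreatment and for the deciding culture. As printed, case d is scored favourable, and case e may be, depending on an unstated timing rule. It is a drafting fault in the primary endpoint, probably affects few participants, and changes no sample-size figure.

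Two stronger readings are not supported:

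- **That the gap biases both comparisons towards non-inferiority.** In Group B, most of the control's time after treatment lies outside item (8). Relapses that escape there raise the B-SOC favourable rate and make non-inferiority of B1 harder to show. The one-month span also comes from a 20-month regimen with follow-up fixed from randomisation, not from item (8) alone. In Group A every arm is planned at 9 months under the same rule, and the net effect is the difference between arms in such cases, which the documents do not allow one to sign.
- **That the loss can be set against the 10-point margin.** Suppose relapse of 3–6%, with 25–50% first found at month 21 and 25–50% of those without a standing positive culture. This gives 0.03 × 0.25 × 0.25 = 0.2 to 0.06 × 0.5 × 0.5 = 1.5 points in an arm. All three inputs are assumptions, and the margin applies to a difference between arms. With relapse of 3% against 6% at the top factors, the difference is 1.5 − 0.75 = 0.75 points.

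**What to change.** Make three changes to Table 4:

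1. Let item (8) count a new RR-TB regimen started after the end of the allocated regimen and up to and including the participant's final outcome assessment (the month 21–23 visit or culture), including a regimen decided at that visit. This closes case d.
2. State that a culture taken after a new RR-TB regimen has started cannot support a favourable outcome.
3. State that an unfavourable classification, once made, is final. With the second change, this closes case e.

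The cost is a few sentences and an update to the outcome algorithm, with no added visits and no change in sample size. Favourable rates may fall slightly. Group A was still recruiting in September 2025 and Group B enrolment was complete. The change should therefore be dated and made without reference to outcomes by arm.
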